#### 6.4 Sample Size

After enumerating the full retrospective cohort, we will randomly select eligible HIV-positive women and their HEIs for our nested cohort. For this nested cohort, our sample size will be determined by a power calculation for our primary outcome of interest—maternal retention in care 12 months after ART initiation. For this calculation (*see summary in Table 2 below*), we assume that 75% of MIPs receive services from a CFL model of interest in our selected districts, and that approximately 73% of HIV-positive mothers receiving the SOC will be retained in care at 12 months post-ART initiation (based on the most recent, first quarter 2017 data from the Malawi national program). With a two-sided alpha of 0.05, we will have 80% power to detect a programmatically meaningful 8% difference in the proportion of mothers retained in care between those who do and do not receive CFL services by enrolling 894 mothers from CFL sites and 298 mothers from SOC sites into our nested cohort (for a total of 1,192 mothers). Assuming that approximately 75% of HIV-positive mothers in SOC sites will be virologically suppressed (a weighted composite of 88% suppression among the 73% of HIV-positive mothers in care and approximately 40% suppression among the 27% of HIV-positive mothers not in care), we will have 83% power to detect a 8% difference in the proportion of HIV-suppressed mothers between those who do and do not receive CFL services. Finally, assuming that we will enrol about one HEI for every mother in the nested cohort, and that 92% of all HEIs not receiving CFL services (i.e. receiving SOC) are alive and HIV-free at 12 months (based on published data that 7% of HEIs become HIV-infected by 12-months and 96% of HIV-exposed but *uninfected* infants are alive at 12 months), we will have 90%

power to detect a 5% difference in HIV-free survival between HEIs who do and do not receive CFL models of interest by recruiting 1,192 total HEIs..

| Table 2: Summary of power and sample size calculations for primary outcomes of interest. |                                 |                    |              |                                 |                                 |

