#### **6.5.2.2 First Stage Data Collection: Chart Review**

In the first stage of data collection, we will seek out outcome information for all MIPs in the full retrospective cohort by abstracting existing clinical and demographic data from routine MOH treatment cards and registers and from electronic medical records (where available) at our 40 selected facility catchment areas. Study staff will have no direct contact with MIPs in the retrospective cohort, apart from those MIPs selected to potentially participate in the nested cohort.

Information to be abstracted will include such data as: HIV testing history, 6-, 12-, and 24-month post-ART initiation maternal vital status (e.g. alive in care, transferred out, stopped ART, died, and lost to follow-up); 6- and 24-month maternal viral load (timing per national guidelines); exposed-infant first HIV-1 DNA PCR result (from 6 weeks of age per national guidelines); 12- and 24-month HEI vital status (including death); and 12- and 24-month HEI HIV sero-status (timing per national guidelines). We will also abstract the first documented DNA PCR test result for all HEIs from HCC registers and treatment cards and laboratory records, which will include results for samples taken at 6 weeks of age and later, including “late” test results for HEIs who enrolled into follow-up after 6 weeks of age. Similarly, many HIV-exposed children undergo their 12- and 24-month rapid tests after these time points due to late presentation to clinic for “milestone” visits, HIV test kit stock outs, and other reasons. As a result, the “median age at first HIV rapid testing” may be closer to 15 or 18 months than the recommended 12 months, providing valuable information about HEI HIV status at or near the conclusion of breastfeeding. Because HEIs enrolling into routine HIV care through June 30, 2017 are eligible to join the full retrospective cohort, some HEIs will not reach age 24 months before administrative censoring (anticipated to take place between end 2017 and end 2018, depending on the district). The 12-month calendar period for cohort construction was selected to maximize power for the primary outcome (i.e. 12-month maternal HIV retention in care). 24-month outcomes for infants who are censored before reaching age 24 months will be represented by those who are observed at age 24 months and by a simple sensitivity analysis (*see section 7.0 Data Analysis*).

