### **6.5.2.3 Second Stage Data Collection**

#### *6.5.2.3.1 Nested Cohort Procedures Overview*

Randomly selected nested cohort MIPs will undergo written informed consent, complete a structured questionnaire about their experiences with CFL models and other health services, and undergo one-time HIV testing (i.e. by collecting a dried blood sample [DBS] from the mother for viral load testing and either performing rapid HIV-1/2 antibody testing or collecting a DBS sample on the HEI for HIV infection ascertainment, as indicated based on HEI age per national testing guidelines).

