#### *6.5.2.3.6 Nested Cohort Exposed Infant Biological Outcome Ascertainment*

For HEIs of maternal nested cohort participants, study staff will support routine EID testing procedures at MOH ART/HCC clinics in selected districts according to national guidelines. Thus, for HEIs over 6 weeks but under 12 months of age who are without a documented DNA PCR test result at the time of study field activities, we will collect a routine DBS sample for “catch up” DNA PCR testing to be performed through the existing MOH EID testing system. Similarly, for HEIs 12 months of age and older without a documented HIV rapid test result, we will support “catch up” infant rapid HIV serological

testing through review of existing MOH records and referral of HEIs with unknown status for HIV testing services (HTS).

For HEIs of nested cohort participants who are over 6 weeks but under 12 months of age, and who have previously undergone MOH EID testing but who are without a documented HIV test result within about 3 months of their mother's study encounter, we will collect 1 DBS card sample (i.e. 5 wells of 50 µL each or 250 µL total) following MOH-recommended collection procedures for study-specific DNA PCR testing to be done at the UNC Project Tidziwe Laboratory in Lilongwe. For HEIs 15 months of age or older who have not received routine HIV testing within about 3 months of their mother's study encounter, study staff will conduct study-specific HIV rapid antibody testing in accordance with MOH HTC procedures.

In all cases, we will follow MOH guidelines for HIV testing, including the preparation, collection, handling and transport of DBS samples for EID testing. All EID DNA PCR test results will be returned to the clinic from which the HEI was originally identified. We will subsequently inform all mothers that their HEI's test results are ready and have been submitted to the clinic. We will recommend they return to discuss these results with the clinic healthcare providers. This will support good clinical care and will also provide additional encouragement to those disengaged/ defaulted from care to re-engage.

Due to the dispersion of HEI ages at the time of maternal and infant enrolment in the nested cohort, it will not be possible to ensure testing at a pre-specified age. We will adjust for any variability in timing of HIV testing during the analysis phase (*see section 7.0 below*).

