## **7.2.2 Analysis Plan for Objective 2 & 2a**

### **7.2.2.1 Cohort Data**

We will calculate maternal retention in care as the proportion of mothers alive and in care at 6, 12, and 24 months post-ART initiation among all eligible women at the start of the cohort. We will also calculate median days from PMTCT enrolment to ART start to examine the effects of CFL models on time to ART initiation. We will look for differences in the delay of ART initiation across the CFL models and SOC using the Aalen-Johansen estimator to account for the competing event of death. We will report crude HEI mortality at 12 and 24 months as part of our survival analysis. We will define infant 12-month HIV free survival as the proportion of HEIs alive with a negative 12-month HIV-rapid test among all infants enrolled in the HEI birth cohort. Similarly, we will define infant 24-month HIV free survival as the proportion of HEIs alive with a negative 24-month HIV-rapid test among all infants enrolled in the HEI birth cohort. We will use Kaplan Meier techniques to compare infant HIV-free survival at 12 and 24 months across the 3 CFL models and SOC accounting for informative censoring and differences in baseline patient characteristics between the models using inverse probability weights. We will censor all survival outcomes on the last date of field activities in a given district (most likely between February 1, 2018 and April 30, 2019, depending on the district), the date of transfer, or the date of the last clinical encounter, as appropriate.

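### Infant 12-month HIV-free survival is scored on one rapid antibody test, with no rule for a reactive result that later proves negative

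*Protocol*

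**What the plan says.** - **Outcome.** Section 7.2.2.1 counts as HIV-free survivors "the proportion of HEIs alive with a negative 12-month HIV-rapid test among all infants enrolled in the HEI birth cohort". It does not mention confirmed status or discordant results.
- **Type of test.** Section 6.5.2.3.1 describes the choice for the infant, by age, as "performing rapid HIV-1/2 antibody testing or collecting a DBS sample on the HEI for HIV infection ascertainment". In section 6.5.2.3.6, DNA PCR is used under 12 months. Catch-up rapid serology applies "for HEIs 12 months of age and older without a documented HIV rapid test result". From 15 months, if there is no recent routine test, "study staff will conduct study-specific HIV rapid antibody testing in accordance with MOH HTC procedures".
- **Guidelines.** Section 6.5.2.3.6 adds: "In all cases, we will follow MOH guidelines for HIV testing, including the preparation, collection, handling and transport of DBS samples for EID testing". The content of those guidelines is not reproduced.
- **Timing.** Section 6.5.2.2 says the median age at first rapid test "may be closer to 15 or 18 months than the recommended 12 months". Section 6.5.2.3.6 promises for infants: "We will adjust for any variability in timing of HIV testing during the analysis phase". Section 7.2.2.1 names a method for variable test timing only for maternal viral suppression. Its infant exclusion and weighting rules for incomplete follow-up concern 24 months.
- **Planning.** Section 6.4 starts from infection, citing that "7% of HEIs become HIV-infected by 12-months". It plans 92% against 97% HIV-free survival with 298 SOC and 894 CFL infants, two-sided alpha 0.05 and 90% power.
- **Status of the outcome.** Section 7.1 lists it as secondary. The caption of Table 2 places it among the primary outcomes of interest.

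**The concern.** The quantity of interest is infection, but the scoring rule measures antibody. Section 7.1 itself separates HIV-free survival from infant sero-status and ties early infection status to a DNA PCR result, so the distinction is one the protocol already makes.

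An infant born to an HIV-positive mother can carry her antibody without being infected, and this can last to around the first birthday. That is general knowledge; the protocol does not state it. Under the rule as written, such an infant is a failure even if a PCR on the same day or a rapid test some months later is negative. The planned Kaplan-Meier comparison would inherit the problem, because a reactive test would enter as an event.

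At stake are the level of the estimate and the power of the comparison. With true infection near 7%, a small share of false reactives is a large share of all positives. Even if the error is equal in both groups, it lowers both proportions, adds variance and slightly narrows the difference.

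**Working it through.** **Inputs from section 6.4.** p1 = 0.92 (SOC), p2 = 0.97 (CFL), n = 298 SOC, ratio k = 3 (894 CFL), two-sided alpha 0.05, infection 7%. The 92% is taken as stated.

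**Input not in the protocol.** f is the share of living, uninfected infants who are reactive at the scored test and whose result is not resolved. Assumed values are 1%, 2%, 5% and 10%.

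**Step 1: reproduce the stated power.** For two proportions with pooled variance,

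power = Φ{ [d√n − 1.96·√(p̄(1−p̄)(1+1/k))] / √(p1(1−p1) + p2(1−p2)/k) }.

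- d = 0.05 and p̄ = (0.92 + 3 × 0.97)/4 = 0.9575.
- d√n = 0.05 × 17.263 = 0.863.
- 1.96 × √(0.9575 × 0.0425 × 4/3) = 0.457.
- Denominator: √(0.0736 + 0.0097) = 0.289.
- Power = Φ(1.41) = 92.1%.

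With the continuity correction, power is 89.9%, which matches the stated 90%. The figures below omit the correction, so their baseline is 92.1%. Like the plan's own figure, they make no allowance for clustering or weights.

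**Step 2: same f in both groups.** Observed proportion = true proportion × (1 − f).

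| f | SOC | CFL | Difference (points) | Power |
|---|---|---|---|---|
| 0 | 92.0% | 97.0% | 5.00 | 92% |
| 1% | 91.1% | 96.0% | 4.95 | 87% |
| 2% | 90.2% | 95.1% | 4.90 | 83% |
| 5% | 87.4% | 92.2% | 4.75 | 68% |
| 10% | 82.8% | 87.3% | 4.50 | 50% |

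**Step 3: share of positives that are false.** Ignoring deaths, this is 0.93f / (0.93f + 0.07).

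- f = 1%: 0.0093/0.0793 = 12%
- f = 2%: 0.0186/0.0886 = 21%
- f = 5%: 0.0465/0.1165 = 40%
- f = 10%: 0.0930/0.1630 = 57%

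**Step 4: can the direction between groups be fixed?** Suppose f applies only to tests done on time, and take f = 5%.

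- On-time shares of 30% SOC and 60% CFL: 0.97 × (1 − 0.05 × 0.60) − 0.92 × (1 − 0.05 × 0.30) = 94.1% − 90.6% = 3.5 points.
- Shares reversed: 95.5% − 89.2% = 6.3 points.

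Read literally, the same definition also fails a living infant with no test. If 73% of SOC and 80% of CFL infants were tested (an assumption that borrows Table 3's shares of mothers with complete routine data), the observed values would be 0.92 × 0.73 = 67.2% and 0.97 × 0.80 = 77.6%. That is a difference of 10.4 points in favour of the better-tested group. The protocol gives neither timing nor testing shares by group, so the sign of the net bias is open.

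**The case against.** **National guidelines may already resolve reactive results.** Section 6.5.2.3.6 follows them throughout, and infant status is abstracted from routine records, so some recorded statuses may already be final ones. This limits how many infants are affected. It does not change section 7.2.2.1, which scores the 12-month rapid result and not the resolved status.

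**Timing will be adjusted for.** The promise is specific to exposed infants, but section 7 does not carry it out for the 12-month infant outcome. Adjusting for age at test would in any case not reclassify a false reactive.

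**Testing is expected to be late.** This stands. A median near 15 or 18 months would put fewer than half of first rapid tests near 12 months, and study-specific rapid testing starts only at 15 months. The higher values of f are then less plausible as cohort averages.

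**Discordant results belong in the analysis plan.** A missing detail could wait for that document. Here the protocol fixes the definition, and it is the fixed wording that misclassifies.

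**A stronger reading that does not hold.** A reader might infer that the error runs against CFL sites, because they would test more infants on time. For example, with 70% of CFL and 40% of SOC infants on time, the artefact is 0.92 × 0.30 × (reactivity at 12 months − reactivity at 15 months or later). For reactivity pairs of 2%/0%, 5%/1% and 10%/2% this gives 0.55, 1.10 and 2.21 points. No passage supports that split. It implies 0.75 × 70% + 0.25 × 40% = 62.5% on time overall, which does not fit the expected late median, and the untested-infant effect pushes the other way.

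**Conclusion.** The point holds as a defect in the outcome definition. Section 7.2.2.1 scores an infection endpoint on a single rapid antibody result and lets no later negative result override it. Following the rule as written misclassifies living, uninfected infants with residual maternal antibody.

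The size rests wholly on an assumed reactivity rate. Over 1% to 10%, equal in both groups, the SOC value falls by 0.9 to 9.2 points and power falls from 92% to between 87% and 50%. Late testing would move the truth towards the smaller end. No direction of bias between CFL and SOC can be claimed.

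Maternal 12-month retention, the only primary outcome in section 7.1, is unaffected. The definition should be corrected, but the main result of the study does not depend on it.

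**What to change.** In section 7.2.2.1, define 12-month HIV-free survival by confirmed infection status, from data already abstracted or collected:

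- A negative rapid test in a living infant remains a success.
- A reactive rapid test near 12 months is scored uninfected if a DNA PCR taken at or after it is negative, or if a later rapid test is negative (the study test from 15 months, or the 24-month sero-status). An earlier negative PCR does not suffice, because infection through breastfeeding could follow it.
- A reactive result that a later result confirms is scored infected.
- With no later result, status is unknown and is handled by the inverse probability weights already planned. A sensitivity analysis scores these infants once as infected and once as uninfected.

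No new testing procedure or age cut-off is needed. The study DBS PCR in section 6.5.2.3.6 is described only for infants under 12 months, and this rule does not extend it.

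The cost is a change of wording, some extra abstraction (section 6.5.2.2 singles out the first PCR result, so later ones must be captured too) and a few infants with unknown status. Most of these would be outside the nested cohort, where study staff have no contact with the pairs.

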## **6.5.2 Study Procedures for Objectives 2 & 2a**

### **6.5.2.1 Objectives 2 & 2a Overview**

In “real-world” PMTCT programmatic settings where the absolute numbers of MIPs is large, prospectively ascertaining clinical outcomes, including maternal viral load and infant/young child HIV status, is often challenging for an implementation research study such as this one. Therefore, we will learn about MIP health outcomes using an efficient, two-stage cohort design.

In the first stage, we will retrospectively construct a cohort of HIV-infected women entering the national PMTCT program and receiving community-facility linkage (CFL) services or the SOC between July 1, 2016 and June 30, 2017 in our 40 randomly selected facility catchment areas. For all areas, we will review existing, routine MOH data for all eligible women and their infants to abstract retrospective data on our outcomes of interest—12-month maternal retention in care, viral suppression for HIV-positive mothers, and 12-month infant HIV-free survival. (Of note, maternal and infant outcomes have two different “starting points” for determining the 12-month outcome, which we will account for in our analysis—in the case of HIV-positive mothers the “starting point” is ART initiation date and for infants it is date of birth).

In the second stage, we will use epidemiological sampling to obtain outcomes on a nested cohort of approximately 1,200 randomly selected MIPs drawn from the full retrospective cohort (*see section 6.4 Sample Size*). Information will be collected from these 1,200 participating MIPs through a detailed questionnaire and blood sampling for maternal viral load and infant HIV testing, and will be enriched by qualitative in-depth interview (IDI) data for 60 women purposively selected from among the MIPs in the nested cohort. IDIs will explore maternal perceptions, experiences, and satisfaction with CFL models and services, including with their key components, and how these services have affected their longitudinal engagement with and retention in the national ART program.

Data from the first and second stages will be combined to present the HIV care cascade for MIPs in aggregate, and by CFL model/ SOC, from HIV testing through ART initiation and viral suppression. Uptake of HIV services at the three main steps of the HIV care cascade will be calculated according to UNAIDS definitions and compared against established “90-90-90” benchmarks (*see section 7.2.2.2 below*).

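### Infant HIV-free survival is defined among enrolled infants with the clock at birth, and no text returns never-enrolled infants or pre-enrolment deaths to the denominator

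*Protocol*

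**What the plan says.** Section 7.2.2.1 defines the 12-month infant outcome as the share of exposed infants who are alive and rapid-test negative at 12 months "among all infants enrolled in the HEI birth cohort", and words the 24-month outcome the same way. In the same paragraph, maternal retention is taken "among all eligible women at the start of the cohort".

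The term HEI birth cohort is not defined anywhere in the protocol. The nearest statement of how infants enter is in section 6.5.2.2: "HEIs enrolling into routine HIV care through June 30, 2017 are eligible to join the full retrospective cohort". That section also expects late entrants, referring to "HEIs who enrolled into follow-up after 6 weeks of age". Section 6.5.2.1 fixes the time origin: "for infants it is date of birth".

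Other parts speak of all infants. In section 6.5.2.1, "we will review existing, routine MOH data for all eligible women and their infants to abstract retrospective data on our outcomes of interest". Section 6.4 bases the infant power calculation on the assumption that "92% of all HEIs not receiving CFL services (i.e. receiving SOC) are alive and HIV-free at 12 months".

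**The concern.** Enrolment into infant follow-up happens after birth and after the mother has been exposed to a CFL model or to the standard of care (SOC). A denominator that requires it conditions on a step that the exposure may change. Two consequences follow if unenrolled infants fare worse:

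- HIV-free survival among enrolled infants is higher than among all infants born to cohort mothers, in every group.
- A CFL model that brings more of the high-risk infants into follow-up keeps their deaths and infections in its denominator, whereas the SOC group loses them. The model's benefit is then understated.

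The protocol's own background makes both conditions plausible. Section 3.0 reports better return for early infant testing with mentor mothers and better infant testing with a community health worker programme. Section 2.0 has CFL providers tracing infants who fall out of care, and links drop-out to more transmission and worse outcomes. None of this is a measurement of infant enrolment by model.

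**Working it through.** **1. The plan's own figure.** Section 6.4 and Table 2: 92% versus 97%, 298 SOC and 894 CFL infants, two-sided alpha 0.05, power 0.90.

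- Pooled proportion: (0.92 + 3 × 0.97)/4 = 0.9575
- Null SE: √[0.9575 × 0.0425 × (1/298 + 1/894)] = 0.0135
- Alternative SE: √[0.92 × 0.08/298 + 0.97 × 0.03/894] = 0.0167
- Power without continuity correction: Φ[(0.05 − 1.96 × 0.0135)/0.0167] = 0.92
- Power with continuity correction, subtracting ½(1/298 + 1/894) = 0.0022 from 0.05: 0.899

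The stated 0.90 reproduces with the correction. The point does not rest on an error in that figure.

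**2. Which infants the text admits.** The section 7.2.2.1 definition requires enrolment. The section 6.5.2.2 entry rule is enrolment into routine HIV care. The inverse probability weights for the Kaplan-Meier comparison cover informative censoring and baseline differences; an infant who never enters is not censored. The sampling weights later in section 7.2.2.1 cover selection of the site, selection of the pair, and participation. None of these concerns entry to the infant denominator.

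**3. Size, under assumptions.** Let H be HIV-free survival among all births, u the share never enrolled, and h HIV-free survival among the unenrolled. The enrolled-only estimate is

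(H − u·h)/(1 − u).

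The protocol gives H = 92% (SOC) and 97% (CFL) as planning values. It gives neither u nor h; the values below are assumed, with the same h in both groups and no recovery of unenrolled infants in stage two.

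| True SOC / CFL (%) | u, SOC / CFL | h | Observed SOC (%) | Observed CFL (%) | CFL − SOC (points) |
|---|---|---|---|---|---|
| 92 / 92 | 10% / 5% | 0.80 | 93.3 | 92.6 | −0.7 |
| 92 / 92 | 10% / 5% | 0.50 | 96.7 | 94.2 | −2.5 |
| 92 / 92 | 20% / 5% | 0.70 | 97.5 | 93.2 | −4.3 |
| 92 / 92 | 5% / 5% | 0.80 | 92.6 | 92.6 | 0 |
| 92 / 97 | 10% / 5% | 0.80 | 93.3 | 97.9 | +4.6 |
| 92 / 97 | 10% / 5% | 0.50 | 96.7 | 99.5 | +2.8 |
| 92 / 97 | 20% / 5% | 0.70 | 97.5 | 98.4 | +0.9 |
| 92 / 97 | 5% / 5% | 0.80 | 92.6 | 97.9 | +5.3 |

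First row in full: SOC (0.92 − 0.10 × 0.80)/0.90 = 0.933; CFL (0.92 − 0.05 × 0.80)/0.95 = 0.926.

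Three things follow.

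- Absolute survival is overstated in every row. In the SOC group with 10% unenrolled, the excess is 1.3 to 4.7 points.
- With equal non-enrolment of 5% the comparison is unbiased under no effect, and 0.3 point too large under the planned effect.
- At 10% versus 5% unenrolled the harm is to the estimate rather than to power, which stays near 0.90 to 0.93 without continuity correction because both proportions move towards 1. At 20% versus 5% with h = 0.70, the remaining 0.9-point difference has power of about 0.20.

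**The case against.** The strongest reply is that the study's second stage already deals with this. Mothers, not infants, are the sampling frame for the nested cohort, whatever their care status (section 6.5.2.3.2). Their infants are offered catch-up testing or referral, with no stated condition of prior enrolment (section 6.5.2.3.6). Lost pairs are traced (section 6.5.2.3.8). Section 7.2.2.1 says that traced pairs are included and that all estimates are corrected to the sampled pairs. The abstract lists vital status of mother and infant among the stage-two outcomes. The infant power calculation also belongs to this mother-based sample. In addition, a birth cohort could be read as all infants of cohort mothers followed from birth.

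Much of this stands. The reading of the undefined term is an inference from section 6.5.2.2, and exclusion is firm only for the definition as written and the chart-review stage. What the reply does not supply is a sentence placing a traced infant who never enrolled, or who died before enrolment, in the denominator of section 7.2.2.1. Next-of-kin data are specified for a dead patient, and the questionnaire topics in section 6.5.2.3.4 name no delivery outcome or infant death, although that list is not exhaustive.

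Direction is also not settled. Section 6.5.2.3.7 describes enrolment of all exposed infants as routine care, so enrolment may differ little by model. Infants who enrol late have by definition survived until then, which flatters whichever group enrols later.

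A reader might infer that never-enrolled infants are lost from every infant estimate and that CFL models will look worse by some definite amount. For example, 92% HIV-free among enrolled SOC infants, 75% among the unenrolled, and enrolment of 80% under SOC and 95% under CFL give (0.80 × 0.92 + 0.15 × 0.75)/0.95 = 89.3% against 92.0%, or −2.7 points. The documents do not support that as a finding. The enrolment figures are invented, stage-two recovery is set to nil, and section 6.4 states its 92% for all exposed infants rather than for enrolled ones.

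**Conclusion.** The point holds as a defect in how the outcome is fixed. The written denominator requires enrolment, the clock starts before it, the maternal outcome and the power calculation do not share the restriction, and no stated weight or rule corrects for entry. Absolute infant HIV-free survival would be overstated if unenrolled infants do worse. The comparison can be biased against a CFL model if, in addition, that model enrols a larger share of infants; with equal enrolment it is little affected.

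The size cannot be derived from the protocol. The range of about −0.7 to −2.5 points under no true effect assumes 10% versus 5% unenrolled and 80% to 50% HIV-free survival among them, with no recovery through tracing. Neither certain exclusion of these infants nor a particular spurious difference is established. Section 7.1 lists the outcome as secondary, although Table 2 powers it under a primary-outcome title, so the change should be made but does not threaten the maternal primary analysis.

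**What to change.** In section 7.2.2.1:

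- Replace the denominator for both infant outcomes with all live-born infants of eligible cohort mothers, followed from birth, without requiring enrolment in exposed-infant follow-up, and align the entry rule in section 6.5.2.2.
- Count deaths before enrolment as events.
- State that never-enrolled infants and early deaths found in the nested cohort are included, using the sampling and participation weights already specified there.
- Report the share of infants enrolled and age at enrolment by CFL model and SOC.
- If any analysis is limited to enrolled infants, allow for delayed entry and say that deaths before enrolment are not captured.

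The cost is small: one item on delivery outcome and infant vital status, from records or the questionnaire already administered, and more missing routine infant data to handle by weighting.
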